## Abstract

**Background:**

CTO-PCI is generally successful, but 40–55% of patients experience coronary microvascular dysfunction (CMVD) afterward, raising the risk of cardiovascular issues. Shexiang Baoxin Pill (SBP) aids angiogenesis and cardiovascular health, while exercise rehabilitation boosts coronary collateral circulation. However, the combined impact of these treatments on CTO-PCI patients remains under-researched.

**Methods:**

This prospective, single-center, randomized controlled trial involves CTO-PCI patients divided into four groups: Shexiang Baoxin pill, exercise rehabilitation, combined, and control. The exercise protocol includes pre-assessment, a three-phase prescription, CPET-based intensity grading, various exercise methods, remote monitoring, and quality control. The primary outcome is coronary microcirculation assessed by myocardial contrast echocardiography and stress myocardial perfusion imaging 1-year post-surgery. Secondary outcomes include angina incidence, major adverse cardiovascular events (MACE), quality-of-life improvements, and mechanism-related biological indicators, with safety outcomes monitoring liver and kidney function. Data will be analyzed statistically.

**Discussion:**

This study will demonstrate the positive effects of Shexiang Baoxin pill combined with exercise rehabilitation training in improving coronary microcirculatory conditions, reducing major adverse cardiovascular events, and improving quality of life in patients with CTO-PCI. The results of this study will provide new insights into the CTO-PCI patients’ long-term rehabilitation.

**Clinical trial registration:**

ITMCTR2025000965, Effect of Shexiang Baoxin Pill combined with exercise rehabilitation training on the long-term prognosis of patients with CTO-PCI, Registered on 28 February, 2025.

## Background

1

Coronary chronic total occlusion (CTO) percutaneous coronary intervention (PCI) remains a cornerstone in revascularization strategies, with contemporary studies demonstrating improved procedural success rates exceeding 90% in experienced centers (1). However, long-term outcomes remain concerning, as 40–55% of patients develop coronary microvascular dysfunction (CMVD) post-PCI, significantly increasing risks of recurrent ischemia and major adverse cardiovascular events (MACE). According to a meta-analysis’s subgroup analysis, 36.04% of patients with chronic coronary syndrome (CCS) experience CMVD following PCI (2). About 17.86% of patients with CCS had CTO (3). Numerous studies have established a strong link between CMVD and an increased risk of cardiovascular events (4). For example, in patients with ST-segment elevation myocardial infarction (STEMI), CMVD is common and is closely associated with left ventricular diastolic dysfunction, functional left ventricular remodeling (FLVR), and MACE (5). In obese patients, CMVD not only correlates with an elevated risk of adverse cardiovascular events but also serves as a more robust predictor than body mass index (BMI) (6). This disparity between high procedural success and suboptimal long-term outcomes presents an acute clinical challenge. Although we are proficient in reopening occluded epicardial arteries, protecting the fragile microvasculature from ischemia–reperfusion injury remains a significant hurdle. Addressing this challenge requires further exploration of diagnostic and therapeutic approaches to manage patients at high risk of CMVD-related complications.

Shexiang Baoxin pill (SBP), a representative formulation of traditional Chinese medicine, demonstrates its therapeutic efficacy through the synergistic action of multiple constituents. Artificial musk improves blood circulation and reduces myocardial ischemia. Ginseng boosts qi, modulates the immune system, and supports heart function. Suhexiang aids qi circulation and pain relief, helping alleviate angina symptoms. Calculus Bovis, Bufonis Venenum, and Cinnamomi Cortex clear heat and detoxify, while Borneolum Syntheticum enhances delivery of all components. Recent pharmacological research has substantiated that SBP facilitates the release of nitric oxide by vascular endothelial cells, leading to the dilation of coronary arteries and an increase in coronary blood flow (7). It also inhibits inflammatory cytokines, thereby reducing vascular wall inflammation and stabilizing atherosclerotic plaques. Additionally, the pill promotes angiogenesis, establishing collateral circulation for ischemic myocardium and enhancing myocardial blood supply (8). By improving vascular endothelial function, it aids in the release of vasodilatory substances such as nitric oxide, thereby enhancing blood flow (9). Furthermore, it suppresses vascular wall inflammation by reducing the infiltration of inflammatory cells and the release of harmful mediators, thus slowing the progression of atherosclerosis (10). The pill also encourages therapeutic angiogenesis, stimulating the growth of new blood vessels to support the ischemic myocardium. Its active components, including muscone and ginsenosides, enhance endothelial nitric oxide synthase (eNOS) coupling, reduce nod-like receptor pyrin domain containing 3 (NLRP3) inflammasome activation, and promote VEGF-mediated angiogenesis (11, 12).

Exercise rehabilitation is crucial for managing coronary heart disease by improving coronary artery collateral circulation and microcirculation (13). Regular physical activity strengthens alternative blood flow pathways and enhances oxygen and nutrient delivery to the heart muscle (14). Furthermore, structured exercise rehabilitation has been shown to confer significant microcirculatory benefits through mechanisms such as shear stress-mediated endothelial repair and the activation of the hypoxia-inducible factor 1α (HIF-1α) pathway (15). A meta-analysis of multiple randomized controlled trials has demonstrated that exercise rehabilitation reduces the risk of major cardiovascular events, such as heart attacks and strokes, by 28% in patients with coronary heart disease (16–18). Another study assessed the comparative benefits of cardiac rehabilitation strategies through a Bayesian network meta-analysis, revealing that exercise-only cardiac rehabilitation was associated with decreased cardiovascular mortality and major adverse cardiovascular events (19). Despite these advancements, there is limited research on combining SBP and exercise rehabilitation for those undergoing CTO-PCI. The 2023 ESC guidelines recommend microvascular protection but do not provide specific protocols for integrative approaches. This gap in knowledge hinders the personalized management of high-risk CMVD patients.

The combined use of SBP and exercise rehabilitation offers synergistic benefits, particularly in improving myocardial blood supply. SBP promotes angiogenesis, increasing coronary microvessel number and diameter, while exercise rehabilitation enhances collateral circulation, boosting blood perfusion efficiency in both new and existing microvessels. This integrated approach is more effective in mitigating myocardial ischemia. We suggest that synchronizing SBP with exercise rehabilitation enhances therapeutic outcomes through three aspects: (1) improved coronary microcirculatory function; (2) reduced major adverse cardiovascular events within a year; and (3) enhanced patient quality of life. This study introduces an integrative model for post-PCI microvascular rehabilitation, merging traditional Chinese medicine’s systemic regulation with Western exercise physiology’s biomechanical precision, marking a shift from fragmented approaches. Successful validation could reshape international guidelines, providing the first Class I recommendation for combined pharmaco-mechanical CMVD management.

## Methods

2

### Study design

2.1

This study is a prospective, single-center, randomized controlled clinical trial. Patients with CTO who underwent PCI in the cardiology department of our hospital. Using a computer-generated block randomization sequence (block size = 4), participants were allocated in a 1:1:1:1 ratio to one of four parallel groups: the SBP group, the exercise rehabilitation group, the combined SBP and exercise rehabilitation group, and the control group. Allocation concealment was ensured by a central randomisation module embedded in the Hospital Information System (HIS); the treatment assignment was automatically released only after the participant had been registered and baseline data entry was completed. Figure 1 shows the details of the study process. This study will strictly adhere to the Standard Protocol Items: Recommendations for Interventional Trials (SPIRIT) reporting standard (20).

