### Intervention measures

2.3

As an interventional trial, blinding of participants, treating physicians, and researchers directly involved in intervention implementation was not feasible due to the specific nature of the interventions (including oral SBP and exercise rehabilitation training), whose distinct characteristics would render blinding impractical. Importantly, outcome assessors responsible for data collection and statisticians conducting post-data-collection analyses remained blinded to group allocation throughout the study.

If a participant learns their group assignment during rehabilitation exercises, they will be assessed. If this knowledge could influence their behavior, they may be excluded from the study. Additionally, other participants will be monitored for information leaks. If others are affected, measures like re-evaluating data validity or exclusion from the study will be taken.

Tables 1–6 show the details content of the pre-exercise assessment, the three-phase exercise prescription, the exercise intensity grading, the type of exercise, the remote monitoring, and the outpatient period training program, respectively. The principles of full-cycle rehabilitation are shown in Figure 2. The schedule in this study is shown in Figure 3.

**Table 1 tab1:** Pre-exercise assessment.

Component	Detailed design
Cardiopulmonary function	CPET to measure VO_2_ peak and anaerobic threshold (AT)
Exercise risk stratification	AACVPR risk stratification criteria (incorporating LVEF, arrhythmia history)
Muscle function evaluation	30-s chair stand test, grip strength measurement
Psychological assessment	Hospital anxiety and depression scale (HADS)
Vascular evaluation	Coronary flow reserve (CFR), index of microcirculatory resistance (IMR, optional)

CPET, cardiopulmonary exercise test; AACVPR, American Association of Cardiovascular and Pulmonary Rehabilitation, LVEF, left ventricular ejection fraction.

**Table 2 tab2:** Three-phase exercise prescription.

Phase	Timeframe	Primary goals	Monitoring	Termination Criteria
Phase I	(Inpatient) 2–7 days post-PCI	Prevent deconditioning	Daily assessment	Chest pain > CCS Class II, SpO2 < 90%
Phase II	(Outpatient) 1–6 months post-discharge	Improve aerobic capacity	Weekly onsite + remote	ST depression ≥2 mm, SBP drop >10 mmHg
Phase III	(Home-based) 7–12 months	Long-term maintenance	Monthly follow-up	New-onset VT/AF

CCS, Canadian Cardiovascular Society, VT’AF, ventricular tachycardia/atrial fibrillation.

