SBP and exercise rehabilitation interact across multiple physiological action pathways; they all exert positive effects on cardiac function, vascular endothelial function, and hemodynamics. Pharmacokinetic aspects: low-to-moderate-intensity exercise enhances whole-body metabolic status, making the environment conducive to drug metabolism. Particularly in the digestive system, compared to intense exercise, low- to moderate-intensity exercise is beneficial for drug absorption; it allows for faster efficacy and a better degree of absorption (40). Moreover, long-term exercise training also increases the activity of liver enzymes, such as cytochrome P450, which break down medications, lowering the risk of drug buildup in the body (41). The study noted that co-administration of these has a significant impact on enhancing cardiac function and improving the quality of life in patients with cardiovascular diseases (33).

This study has the following advantages: in study design, strict adherence to evidence-based medical norms. The generation of random sequences by computer, and complete distribution concealment with opaque envelope seals, raises the credibility of the study findings. In addition to the primary outcome, the Seattle Angina Questionnaire (SAQ) will also be used to evaluate the quality of life of the patients, to comprehensively reflect the impact of the treatment, on the overall state of the patient from the patient’s subjective feelings, to provide a more thorough viewpoint for evaluating the treatment effect. In addition to routine clinical outcomes, this study will also gather multidimensional data on inflammatory factors, angiogenesis-related and exercise-related factors, digging into the mechanism in detail at the molecular level. Nevertheless, this study also has some limitations. The study was conducted in only one tertiary A hospital; all subjects were recruited from a single source, which may affect the stability and extrapolation of the findings. Moreover, data collection during the trial was made more challenging by the 1-year follow-up period and possible high dropout rate, which will make the study less effective.

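### A single stated block size of four for four open-label arms makes one assignment in four predictable to anyone tracking the sequence, and two different concealment methods are named

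*Protocol article*

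**What the plan says.** Section 2.1 (Study design) describes the setting: "This study is a prospective, single-center, randomized controlled clinical trial". On the sequence it says: "Using a computer-generated block randomization sequence (block size = 4), participants were allocated in a 1:1:1:1 ratio to one of four parallel groups". It gives no other block size and mentions no stratification factor.

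On concealment, the same section says: "Allocation concealment was ensured by a central randomisation module embedded in the Hospital Information System (HIS"). It adds that "the treatment assignment was automatically released only after the participant had been registered and baseline data entry was completed".

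Section 2.3 (Intervention measures) states that "blinding of participants, treating physicians, and researchers directly involved in intervention implementation was not feasible", while "outcome assessors responsible for data collection and statisticians conducting post-data-collection analyses remained blinded to group allocation throughout the study".

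The Discussion (Section 3), listing the strengths of the design, credits "complete distribution concealment with opaque envelope seals" and does not mention the hospital system.

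**The concern.** When the block is no larger than the number of arms, a 1:1:1:1 block is simply one ordering of the four arms. After three assignments the fourth is fixed, and after two the third is one of two. In an open-label trial at one centre, past assignments show themselves through the treatment given. Hiding the list does not hide what can be deduced from them.

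The stake is selection at entry. A person who knows or strongly suspects the next arm can decide whether to register a given patient now, later or not at all, for instance by holding back a frail patient when an exercise arm is due. Section 2.2.2 leaves room for this, since limited exercise capacity and poor compliance are matters of judgement. The resulting baseline differences exist before any outcome is measured, so blinded assessors and statisticians cannot remove them.

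The second matter is one of text. A central electronic module and opaque envelopes are different mechanisms with different ways of failing, and each is presented as the concealment method.

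**Working it through.** **Inputs.** Four arms at 1:1:1:1, one stated block size of 4 and one centre (Section 2.1). Participants and treating staff are unblinded (Section 2.3). The article states neither a predictability figure nor a final sample size, so there is no figure to reproduce.

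**Block of 4.** There are 4! = 24 possible orders. For someone who knows the earlier assignments in the block, best-guess success at position k is 1/(number of arms left) = 1/(5 − k):

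| Position in block | Best-guess success |
|---|---|
| 1 | 1/4 |
| 2 | 1/3 |
| 3 | 1/2 |
| 4 | 1 |

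- Fully determined: 1 position in 4 = 25%.
- Expected correct guesses per block: 1/4 + 1/3 + 1/2 + 1 = 25/12 = 2.08.
- Average success: (25/12)/4 = 25/48 = 52.1%, against 25% by chance. Enumerating all 24 orders gives the same values.

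**Exercise versus no exercise.** Two of the four arms contain exercise. The first two assignments in a block are both exercise or both non-exercise with probability 2 × (2/4 × 1/3) = 1/3. In that case the exercise status of the third patient is known, as well as that of the fourth. The share of patients whose exercise status is known in advance is (1/3 + 1)/4 = 33%. The same holds for Shexiang Baoxin pill versus none.

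**Alternatives.** For fixed blocks the guesser is assumed to know the size. For varying blocks each size is drawn with equal probability, and the guesser knows the candidate sizes but not their order, tracks every assignment from the first patient and uses posterior probabilities. That simulation used 400 runs of 200 patients; 200 is an assumption.

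| Scheme | Fully determined | Best-guess success |
|---|---|---|
| Fixed 4 (as stated) | 25.0% | 52.1% |
| Fixed 8, size known | 14.3% | 46.9% |
| Fixed 12, size known | 10.0% | 44.1% |
| Varying 4 and 8 | 7.5% | 48.8% |
| Varying 8 and 12 | 4.6% | 45.1% |

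The main gain from varying blocks of 8 and 12 is in certainty (25% to about 5%). Overall guessing falls only from 52% to about 45%, which lies between the figures for known fixed blocks of 8 and of 12, not below both.

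**Cost in balance.** If recruitment stops inside a block, two arms can differ by at most the number of places per arm in that block: 1 for a block of 4, 2 for 8, 3 for 12.

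**Concealment texts.** Section 2.1 names an electronic module with automatic release after registration and baseline entry. The Discussion names opaque envelopes. Nothing in the article says that both are used or how they would fit together.

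**The case against.** The strongest reply is that prediction is possible in principle but not shown in practice. A reader might infer that recruiting staff are certain of every fourth assignment. The document does not support that. It does not say who recruits or registers patients, or whether they see earlier assignments. Section 2.3 unblinds treating physicians and those delivering the interventions, and does not mention recruiters. Section 2.4 restricts access to the study database. Certainty also needs an unbroken record of assignments and knowledge of where a block starts.

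This limits the claim but does not remove it. The block size is published, patients come from one cardiology department, and Section 2.5.1 describes a follow-up platform and WeChat group that bring clinicians, rehabilitation physicians, patients and families together. Overlap between those who recruit and those who see treatment is plausible, though inferred.

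A reader might also conclude that the trial is unstratified. Section 2.1 is only silent, and the article condenses a protocol that is not shown. Stratification would make tracking harder, but the fourth assignment within each stratum would still be determined. That the block size never varies is likewise read from the single value given.

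Finally, the envelope sentence might be taken as evidence that concealment failed. It is not: it is a general remark in the Discussion set against a specific description in the Methods, and a text correction may be enough once the facts are confirmed.

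**Conclusion.** The point holds as a design weakness with a known size. With the stated scheme, 25% of assignments can be known in advance and 52% guessed, against 25% by chance, by someone who tracks assignments and knows where blocks start. The release rule in Section 2.1 protects the list but not against this inference, and blinded outcome assessment acts too late to help. Whether anyone is in a position to use the predictability cannot be told from the document, so the selection bias is a risk and not an established fact. The figures assume one running sequence with every block of size 4.

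The conflict between the hospital system module and the opaque envelopes is present in the current text and unreconciled. It is the smaller of the two matters.

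**What to change.** 1. For all remaining allocations, have the hospital system module draw from randomly varying larger blocks, for example 8 and 12. An independent statistician should hold the sizes, which should not be disclosed to recruiting or treating staff or printed in documents they see. How many allocations remain cannot be determined from the article: Section 2.1 describes allocation in the past tense, while Section 2.9 says pilot studies to set the sample size are still under way.
2. Confirm which concealment method is actually used, state it in both Section 2.1 and the Discussion, and delete the other.

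The cost is a new list in the hospital system, two corrected sentences, and a possible final imbalance of a few patients between arms.

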**Figure 1 fig1:**
[figure not shown]
The flowchart of the study process.

### Study population

2.2

#### Inclusion criteria

2.2.1

Patients aged >18 years old, regardless of gender, diagnosed with CTO through coronary angiography.

Patients with evidence of myocardial ischemia who are planned to undergo or have successfully completed CTO-PCI.

Patients who can understand the purpose of the study, are willing to participate, sign the informed consent form, and are eager to follow up as required.

Patients with instruments who possess devices that measure fundamental physiological indicators (e.g., electronic blood pressure monitors).

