#### Exercise rehabilitation intervention

2.3.2

Patients in the exercise rehabilitation group will undergo a comprehensive assessment before exercise, including general function assessment, exercise risk assessment, exercise tolerance assessment, and psychological assessment. Then, the exercise intensity will be set according to their individual conditions and cardiopulmonary exercise test results. They will be divided into low-intensity, medium-intensity, and high-intensity rehabilitation groups. The exercise program will include aerobic exercise, resistance exercise, and flexibility exercise. During the hospitalization period (acute phase, phase I), the responsible nurse will guide patients to perform rehabilitation exercises. After discharge, patients will receive early outpatient rehabilitation (stable phase, phase II) and maintenance-phase outpatient rehabilitation. The responsible nurse will conduct weekly telephone follow-ups to monitor and guide patients’ exercise implementation.

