### Data collection and outcome measures

2.4

Eligible patients will be informed of the trial, agree to participate, and voluntarily sign the informed consent form. At the first visit, clinicians will collect basic clinical data of patients, including gender, age, medical history, and medication history. The next day, special personnel will measure patients’ height, weight, waist circumference, and resting blood pressure, and collect fasting venous blood for biochemical tests. In the data collection process, participants are assigned ID numbers, which are used as their identifiers in the system to safeguard their real identities. The collected information is stored in a highly secure database with strict access control, accessible only to the study leader and statistical experts. This ensures effective protection of participants’ privacy throughout the trial. Details of the outcome measures are shown in Table 7.

**Table 7 tab7:** Details of the outcome measures.

Outcome type	Specific content	Evaluation time	Evaluation method
Primary outcome	Evaluation of coronary microcirculation	Immediately and 1 year after revascularization	Myocardial contrast echocardiography (MCE): MBF; myocardial perfusion imaging (MPI): SDS
Secondary outcomes	Incidence of angina pectoris	1 month, 3 months, 6 months, and 12 months after revascularization	Clinical observation and recording
Secondary outcomes	Incidence of MACE during hospitalization, including all-cause death, recurrent myocardial infarction, and target lesion revascularization	Period of hospitalisation after revascularisation	Clinical observation and recording
Secondary outcomes	Incidence of 1-year MACE, including all-cause death, recurrent myocardial infarction, and target lesion revascularization	1 year after revascularization	Clinical observation and recording
Secondary outcomes	Assessment of quality of life improvement using SAQ	Period of outpatient review after discharge	Scoring with the validated Chinese version of the SAQ
Secondary outcomes	Inflammatory factors, angiogenesis-related factors, exercise-related factors	1 month, 3 months, 6 months, and 12 months after revascularization	Biochemical tests: IL-1, IL-6, and TNF; VEGF, Ang, NO, and eNOS; FSTL1 and FGF 21

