Rehabilitation therapist	Possess practical qualification in exercise rehabilitation	a. Phase II rehabilitation: correct exercise postures, guide flexibility training and 4–7-8 breathing technique; b. Phase III rehabilitation support: record standardized exercise teaching videos and upload them to WeChat groups
Cardiovascular SPECIALIST	–	a. Safety control: complete exercise risk stratification for participants during enrollment and exclude high-risk patients; b. Emergency medical support: responsible for evaluation and handling of adverse events during follow-up; c. Medication education: provide patients with detailed medication education before they start taking SBP, including the dosage, frequency, time of administration, possible side effects, and the importance of adherence
Patient’s family	Voluntarily participate and receive training	a. Assist in supervision: remind patients to complete daily training as scheduled; Remind patients to take SBP on time every day according to the prescribed dosage and frequency; b. Emergency training: receive special training on CPR and be able to initially handle emergencies occurring during home-based exercise; c. Feedback communication: keep in touch with the research team (full-time research nurses) and feedback patients’ medication status (whether they take the medicine as required, any abnormal reactions) in a timely manner

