##### Comprehensive safety

2.5.2.3

Before the study, patients will undergo a thorough assessment of cardiovascular, muscular, psychological, and vascular functions to identify risks. Personalized rehabilitation plans will be created from these evaluations, with strict control over the intensity and progress for high-risk patients. Facilities are equipped with first-aid equipment and medications, and medical staff are skilled in first-aid procedures.

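### Entry is open before CTO-PCI and at any time after it, but treatment and the primary outcome are timed from the procedure, and release of the allocation is not explicitly tied to PCI success or the post-PCI scan

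*Protocol article*

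**What the plan says.** **Who may enter.** Section 2.2.1 admits "Patients with evidence of myocardial ischemia who are planned to undergo or have successfully completed CTO-PCI". Success is required only of those whose PCI is already done. No limit is set on time since PCI, and the exclusion criteria (section 2.2.2) do not mention failed, cancelled or remote procedures. Section 2.1 describes the population differently: "Patients with CTO who underwent PCI in the cardiology department of our hospital".

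**When allocation is released.** Section 2.1 states that "the treatment assignment was automatically released only after the participant had been registered and baseline data entry was completed". The entry data listed in section 2.4 are history, body measurements, blood pressure and blood tests. Myocardial contrast echocardiography (MCE) and myocardial perfusion imaging (MPI) are not on that list.

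**What is timed from the procedure.** The pill starts after surgery (section 2.3.1). Phase I exercise is inpatient, on days 2 to 7 after PCI (Table 2). Control patients receive routine post-PCI care (section 2.3.4). The primary outcome is assessed "Immediately and 1 year after revascularization" (Table 7).

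**High-risk patients.** Table 8 has the cardiovascular specialist "complete exercise risk stratification for participants during enrollment and exclude high-risk patients". Section 2.5.2.3 provides for individual rehabilitation plans "with strict control over the intensity and progress for high-risk patients", and Table 3 assigns high-risk patients a training intensity.

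**The concern.** The entry rule and the trial clock do not fit together. Two kinds of patient meet the criterion literally but do not fit the schedule:

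- **Allocated before PCI, and the PCI then fails or is cancelled.** There is no revascularisation from which to count the immediate or the 1-year assessment, and no rule says how the patient is handled.
- **Entered long after a successful PCI.** The inpatient phase has passed and, unless the patient happened to be scanned at the time, so has the immediate baseline. If treatment starts at entry, less than 12 months of it has been given by 1 year after revascularisation. In-hospital MACE, a secondary outcome, would precede allocation and could not be an effect of it.

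Participants and treating staff know the allocation (section 2.3). Decisions about such patients after randomisation would therefore be made with the arm known, which is how post-randomisation exclusions introduce bias. Their missing or undefined primary outcomes would also come on top of the 20% dropout that section 2.9 allows for.

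**Working it through.** **Step 1: the rules side by side.**

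| Item | Section | Reference point | PCI success required? |
|---|---|---|---|
| Eligibility, planned PCI | 2.2.1 | Before PCI | Not stated |
| Eligibility, completed PCI | 2.2.1 | Any time after PCI | Yes |
| Population in the design | 2.1 | After PCI | Not stated |
| Release of allocation | 2.1 | Registration and baseline entry | Not stated |
| Pill | 2.3.1 | After surgery | Not stated |
| Phase I exercise | Table 2 | Days 2 to 7 after PCI | Not stated |
| Control care | 2.3.4 | After PCI | Not stated |
| Primary outcome | Table 7 | Immediately and 1 year after revascularisation | Implied by the time origin |

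The first and third rows conflict. The release of allocation does not resolve the conflict, because the entry data listed in section 2.4 could all be collected before PCI.

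**Step 2: illustration of the size.** The article gives no sample size, effect size or SD, because section 2.9 awaits pilot studies. There is no figure of the plan's own to reproduce.

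Inputs from section 2.9: four groups, two-tailed alpha 0.05, power 90%, dropout 20%.

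Assumed input: a share *f* of randomised patients with failed PCI, taken as 2%, 5% and 10%. The upper value is the limit implied by the Background's "improved procedural success rates exceeding 90% in experienced centers". That is a general figure, not this hospital's rate.

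Method: the four-group comparison is treated as a 3-df test in its large-sample chi-square form. Power of 90% at alpha 0.05 then corresponds to a noncentrality of 14.17.

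- If failures are lost, the noncentrality becomes 14.17 × (1 − *f*).
- If failures are kept and analysed with no treatment effect, it becomes 14.17 × (1 − *f*)².
- The non-evaluable share is 1 − 0.80 × (1 − *f*).

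| *f* | Non-evaluable share | Noncentrality, lost | Power, lost | Noncentrality, kept | Power, kept with no effect |
|---|---|---|---|---|---|
| 0 | 20.0% | 14.17 | 90.0% | 14.17 | 90.0% |
| 2% | 21.6% | 13.89 | 89.4% | 13.61 | 88.7% |
| 5% | 24.0% | 13.46 | 88.3% | 12.79 | 86.5% |
| 10% | 28.0% | 12.75 | 86.4% | 11.48 | 82.2% |

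Per 100 evaluable patients, 100/0.80 = 125 must be randomised with dropout alone. With *f* = 10%, the number is 100/(0.80 × 0.90) = 100/0.72, or 139.

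**Step 3: high-risk patients.** Table 8 excludes them, while Table 3 and section 2.5.2.3 provide for training them. Both cannot hold for the same definition of high risk. On timing, Table 8 places the stratification during enrolment, and section 2.5.2.3 places a full assessment of patients before the study.

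**The case against.** The strongest defence is that section 2.1 already closes the gap. It speaks of patients who have had PCI, and it holds the allocation back until baseline entry is complete. The only stated baseline for the primary outcome is the immediate post-revascularisation scan. If that scan counts as baseline data, neither a failed PCI nor a late entrant without the scan could be randomised, and the word planned merely allows consent before the procedure. Inpatient Phase I and in-hospital MACE also suggest recruitment during the index admission. The flowchart and schedule (Figures 1 and 3), which are not available here, may settle the timing.

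This stands as a plausible reading of intent. It does not remove the conflict between sections 2.1 and 2.2.1. It also depends on the scan being part of baseline entry, which the article does not state and which the list in section 2.4 does not support.

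Three stronger readings are tempting but not supported:

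- **Such patients have no usable endpoint.** Myocardial blood flow and the summed difference score can be measured after a failed PCI, and a late entrant can still have a 1-year scan. What is undefined is the time origin, or the immediate baseline.
- **Everything is tied to successful revascularisation.** The texts refer to surgery, PCI or revascularisation. Success is named only for completed procedures in section 2.2.1.
- **High-risk exclusions fall only on the exercise arms.** A reader might infer this from section 2.3.2: "Patients in the exercise rehabilitation group will undergo a comprehensive assessment before exercise". But that passage goes on to setting exercise intensity, and both Table 8 and section 2.5.2.3 point to assessment of all patients before allocation.

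**Conclusion.** The point holds as a defect in stated rules: sections 2.1 and 2.2.1 disagree on whether PCI precedes entry, and nothing in the article explicitly ties release of the allocation to PCI success, to time since PCI or to the immediate scan. Followed literally, the rules permit randomisation of patients without a defined time origin or immediate baseline. It is not shown that this will happen. If allocation in practice follows successful PCI and imaging, the harm disappears and only the wording needs correcting.

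The size is unknown. The fall from 90% power to between 89% and 86% assumes that 2% to 10% of all randomised patients are lost to failed PCI. The 10% end is a stacked worst case: every patient allocated before PCI, the highest failure rate compatible with a general background figure, and every failure lost. No sample size has been set, so this is not a shortfall in an actual design. The loss of power is modest, and the risk of exclusions made with the arm known matters more.

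The contradiction over high-risk patients is a separate matter and stands whatever the timing of allocation.

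**What to change.** 1. In section 2.2.1, keep consent before PCI but restrict randomisation to patients with successful CTO-PCI in the index admission. Align section 2.1 with this.
2. In section 2.1, have the hospital information system release the allocation only after PCI success is recorded and the immediate post-PCI MCE and MPI results are entered, and before Phase I begins. A failed or cancelled PCI then becomes a screening failure, not a post-randomisation loss.
3. Reconcile Table 8 with Table 3 and section 2.5.2.3 on whether high-risk patients are excluded or trained. Whichever rule the investigators adopt should be applied to all four arms, with the risk stratification recorded before allocation.

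The cost is a revised inclusion line, a check in the existing randomisation module, and slightly fewer patients randomised per patient consented. Because section 2.9 still awaits pilot data, the change can be made before the sample size is fixed.
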